## Abstract

**Introduction:**

Anorexia nervosa (AN) is a severe mental health condition associated with high mortality rates and significantly impaired quality of life. National guidelines outline psychotherapeutic interventions as treatments of choice for adults with AN, but outcomes are limited and therapy drop-out high, resulting in calls for new innovative treatments. The Specialist Psychotherapy with Emotion for Anorexia in Kent and Sussex (SPEAKS) research programme sought to develop the SPEAKS intervention avoiding some difficulties inherent in development of earlier interventions, such unclear hypotheses about change processes. SPEAKS focuses on a core hypothesised maintaining factor (emotional experience) with clear proposed model of change. The current feasibility trial aims to provide an initial test of SPEAKS and inform design of a full randomised controlled trial protocol.

**Methods and analysis:**

This study employs a multisite, single-arm, within-group, mixed-methods design. Up to 60 participants (36 therapy completers) meeting inclusion criteria will be offered the SPEAKS intervention instead of treatment-as-usual (TAU). SPEAKS is a weekly psychotherapy lasting nine to 12 months, provided by trained and experienced eating disorders therapists. All other clinical input remains inline with TAU. Acceptability will be assessed using VAS scales and end of therapy interview. Reach and recruitment, such as recruitment yield, will be monitored. To support sample size estimation and economic estimation, data pertaining to eating disorder-related symptoms will be recorded every 3 months, alongside service usage and intervention-specific measures. Videoed therapy sessions will inform model adherence. Additional analyses coding videoed therapy will test SPEAKS change process hypotheses.

**Ethics and dissemination:**

Ethical approval has been granted by London–Bromley Research Ethics Committee (NHS Rec Reference: 19/LO/1530). Data will be disseminated via high-impact, peer-reviewed journals (Open Access preferred), conferences, service user and charity networks (eg, UK charity BEAT) and through a free open conference hosted by National Health Service Trusts and Higher Education Institutions.

**Trial registration number:**

ISRCTN11778891.

**Trial status:**

Recruitment began on 12 December 2019 and ends on 28 February 2021. All data will be collected and the trial ended by 28 February 2022.

**Protocol version:**

SPEAKS protocol V.3.0 (30 August 2020). Changes were made to the original protocol due to the COVID-19 pandemic. A further set of changes were made to incorporate the measures of change processes, resulting in this being the third version of the protocol.

Strengths and limitations of this studyThis feasibility trial studies a novel psychotherapy for adults with anorexia nervosa (AN), with a focus on emotional change: The Specialist Psychotherapy with Emotion for Anorexia in Kent and Sussex (SPEAKS) intervention.This feasibility study is strengthened by its multi-site trial design, completed in largely ‘research naïve’ National Health Service services, increasing insight into its feasibility and generalisability.The study is limited by its single arm design and non-blinded procedures, which may result in biases such as allegiance effects and does not allow for estimating acceptability of a randomised design.In addition to its feasibility aims regarding the SPEAKS intervention, the trial design includes analysis of the therapeutic change process with wider implications for understanding therapeutic change for adults with AN.The trial has been subject to the challenges imposed by the COVID-19 pandemic including regarding clinical and research engagement.

## Introduction

### Background and rationale

Anorexia nervosa (AN) is a severe mental illness with poor prognosis and the highest mortality rate of any psychiatric disorder.^1^ Early intervention is key, but is impeded by a delay of around 18 months from symptoms emerging to treatment, and with multiple relapses likely.^2^ Caregiving for somebody with severe AN is almost twice as lengthy as for somebody with a physical health disorder (eg, cancer) or other mental health difficulty (eg, psychosis).^3^ Thus significant costs exist financially and emotionally to the individual, family and carers, as well as society as a whole, offering a ‘compelling case for change’ in services and treatment (PricewaterhouseCoopers, p.9).^2^

Most recent NICE guidelines in the UK recommend that psychotherapeutic interventions be considered for adults with AN.^4^ Yet results from randomised controlled trials indicate that outpatient treatments do not out-perform each other or control comparisons^5–9^ with weight-restoration achieved by 20% of patients after 1 year.^7–9^ AN is highly valued by sufferers resulting in poor treatment engagement and high drop-out rates.^10^ Thus there is an urgent need to develop innovative interventions that can engage people with AN,^4 11 12^ while targeting unique factors involved in its development and maintenance.^13^ Emotional experience has long been recognised as a factor in the development and maintenance of AN and is recognised as a promising target area for therapies^14^ and increasingly incorporated into psychotherapy interventions for adults with AN.^5–9^ However, outcomes remain limited and it is unclear to what extent emotional difficulties are targeted by these interventions.^15^

This trial comprises part of the Specialist Psychotherapy with Emotion for Anorexia in Kent and Sussex (SPEAKS) programme which aimed to develop and test in a feasibility study an emotion focused intervention for adults with anorexia (the SPEAKS intervention). This research programme sought to overcome several key difficulties with the development and application of some earlier interventions, such as unsuccessful targeting of variables or lack of clarity on how change is achieved. The SPEAKS programme proposes focussing on a core clearly defined model with one key putative maintaining process (emotional experience in AN) and following an ‘interventionist-causal model approach’.^16^ By developing a new model of the development and maintenance of AN drawn from integration of quantitative and qualitative research, it seeks to ensure an emotions’ focus.^17^ The SPEAKS intervention hypothesises a clear and testable change process to be targeted in therapy (figure 1)^18^; thus affording the ability to examine proposed mechanisms of change enabling further evidence-based development and refinement of the model. This body of work involved close partnering with stakeholders including those with current and past experience of AN, families, therapists and service managers.

**Figure 1 F1:**
[figure not shown]
SPEAKS emotion change process. SPEAKS, Specialist Psychotherapy with Emotion for Anorexia in Kent and Sussex.

### Objectives

This multisite feasibility trial aims to investigate the SPEAKS intervention in the following domains:

Acceptability.Reach and recruitment.Adherence and compliance.Sample size and economic evaluation to establish parameters and financial costs of a potential future efficacy/effectiveness trial.Change process analysis.

We hypothesise that:

SPEAKS will be acceptable to participants and therapists.SPEAKS will meet sufficient reach and recruitment expectations to support progression to full effectiveness/efficacy trial.Therapists and service users will be able to adhere to the therapy model as intended and the research requirementsParticipant change over time will reflect the proposed emotion change process outlined in figure 1.

### Trial design

The SPEAKS study is a multisite, single-armed, within-group mixed-methods design.

## Methods: participants, interventions and outcomes

### Study setting

This feasibility study runs in two outpatient specialist eating disorders services (EDS) within the UK National Health Service (NHS): Kent and Medway All Age EDS at NELFT and Sussex EDS at SPFT.

### Eligibility criteria

#### Service users

Service users are eligible to participate if they:

Are referred into Kent or Sussex EDS and meet service criteria (eg, registered with a local general practitioner).Meet Diagnostic and Statistical Manual 5 Criteria for Anorexia Nervosa or OSFED (Other Specified Feeding or Eating Disorder) of Anorexic type.Are aged 18 or above.Have body mass index (BMI) >15 kg/m^2.^Have sufficient English language abilities to complete a talking therapy.

Service users are excluded if they have/are:

Rated as ‘High Risk’, or as ‘High Concern’ in weight criteria, on the MARSIPAN Guidelines for adults with eating disorders (ie, BMI <15 kg/m^2^; weight loss >500 g for two consecutive weeks)^19^Considerable psychological risk, including active suicidal thoughts and plans.Comorbidity requiring treatment priority.Alcohol/substance use disorder.Participating in another treatment trialDiagnosed Intellectual disability impeding ability to use therapy.Pregnant.

#### Therapists

Therapists are eligible to offer SPEAKS in the trial if they:

Are a specialist eating disorder therapis >3 years experience.Work in Kent All Age EDS or Sussex EDS.Have specialist training in an experiential dialogical self chairwork model (eg, emotion-focused therapy (EFT), schema therapy (ST), compassion-focused therapy).

### Interventions

#### Speaks intervention

SPEAKS is an individual outpatient psychotherapy for adults with AN. Participants receive weekly individual sessions of psychotherapy for 9–12 months with two follow-up sessions within 3 months of completion. SPEAKS is intended to be offered face to face in a clinic setting; however, due to the COVID-19 pandemic video sessions via on an online platform are provided.

SPEAKS is a direct replacement for psychotherapy as usual. Therapists receive fortnightly supervision by supervisors trained in the supervision requirements of SPEAKS. The services at both sites are in the same region of the UK and follow national NHS treatment guidelines. All usual care procedures, including additional interventions such as dietician appointments or inpatient referrals will remain the same, but be reported. People will be removed from the trial if they require immediate inpatient treatment at any point or request removal for any reason, and these data will be reported.

#### Intervention development

The development of SPEAKS is consistent with MRC guidance for complex interventions.^20^ SPEAKS was developed following a clear programme of research to integrate quantitative and qualitative data to achieve an initial model of the presentation (lost emotional self)^17^ and potential necessary elements for therapeutic change (eg, Drinkwater *et al*, in prep). This resulted in a clear hypothesised change process to be targeted in therapy.^17^ SPEAKS is organised into five phases, with associated mechanisms of change and therapeutic ‘tasks’ (see figure 2 for brief overview). The intervention developers (AO, TL nd HS) applied relevant psychological therapy models to target highlighted mechanisms, resulting in an integrative therapy drawing chiefly from EFT and ST. The therapy thus relies on dialogical self theory, and therapeutic tasks are those well established in EFT and ST, such as ‘chairwork’ interventions to enable ‘parts of self’ to communicate.

**Figure 2 F2:**
[figure not shown]
SPEAKS treatment phases. AN, anorexia nervosa; SPEAKS, Specialist Psychotherapy with Emotion for Anorexia in Kent and Sussex.ED= eating disorder

#### Intervention guidebook

The SPEAKS intervention is written up in a guidebook for therapists to follow. It outlines SPEAKS change process, mapping it onto expected ‘phases’ of therapy (figure 2). In each phase, associated hypothesised mechanisms are outlined and ‘therapeutic tasks’ described. The guidebook meets requirements for preliminary feasibility evaluation as outlined in the stage model approach for developing a psychotherapy^21^ and assists intervention adherence.

#### Therapist training and supervision

In additional to background training in an experiential dialogical self model, therapists receive 4 days SPEAKS model and therapy training, with further regular training days organised throughout the trial. Ongoing fortnightly supervision is delivered by SPEAKS developers. Where participants consent, all therapy sessions are video recorded for supervision. Regular reflective practice groups are offered by a SPEAKS developer and psychologist external to the clinical services (TL).

### Treatment fidelity, untoward events and protocol adherence

Reviewing videotaped sessions in supervision ensures competent treatment delivery adhering to the SPEAKS model. This is usual good practice in both EFT and ST supervision models. Case records of each therapy session in client notes outline the phase of therapy, emotions focused on and therapeutic tasks employed.

Usual service standard operating procedures (SOPs) regarding clinical care and risk management will be followed. Any protocol violations impacting delivery of SPEAKS such as admission to hospital will be recorded as per Trust guidance, and also logged in trial records for later reporting. Participants who are admitted to hospital will be withdrawn from the study.

### Outcomes

#### Measures of acceptability

Triangulation of qualitative and quantitative data will address acceptability of SPEAKS to participants and therapists.

##### Qualitative

Participant and therapist lived experience of SPEAKS will be examined using post-intervention semi-structured interviews adapted from the Client Change Interview,^22^ completed by the researcher. Acceptability of aspects of the current and future trial designs are also addressed including use of questionnaires and willingness to be randomised to treatment arms.

##### Quantitative

Acceptability and perceived value of core SPEAKS components will be quantitatively assessed using visual analogue scales created for the study using questions based on the acceptability interview, and rated on a seven-point scale strongly agree to strongly disagree (eg, I think the focus of SPEAKS makes sense for me and my difficulties). Numbers of people who choose to end their therapy because they do not think it is acceptable will also be calculated.

#### Measures of reach and recruitment

Screening of potential participants will be logged, and details of unmet inclusion criteria anonymously recorded. Recruitment yield will be monitored. Where participation is declined, reasons will be anonymously recorded. Completeness of measures at each time point will be reported.

#### Measures of adherence and compliance

Treatment fidelity strategies will be employed consistent with the treatment fidelity checklist,^23^ including a clear intervention description (guide-book) and standardised therapist training. As described, session recordings will enable assessment of adherence to SPEAKS, where consented to. A random selection of therapy tapes will be assessed for fidelity and adherence to the model judged by the intervention developers. They will assess core components of the treatments such as empathy (using the Therapist Empathy Scale^24^), appropriate task selection based on identified tasks markers and appropriate task resolution. Data regarding treatment length, session numbers and content will be reported.

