#### Measures of SPEAKS Change Process

The following analyses will test hypothesised therapeutic change process.

Videoed therapy sessions will be analysed according to two coding systems to better understand change associated with better clinical outcomes, including hypotheses about both content and order of change. The Innovative Moments Coding System^35^ is a systematic reliable method for identifying innovative moments (IMs) in therapy, categorising by type (action, reflection, protest, reconceptualisation, performing change). IMs are measured by the percentage of time spent elaborating on each IM (temporal salience). The Classification of Affective Meaning States (CAMS)^36^ codes the presence of emotions expressed during therapy videos in) 1 min segments. The CAMS includes nine emotion categories: global distress (rejecting anger, fear/shame, negative self-evaluation, unmet need, relief, assertive anger/self-compassion, hurt/grief, and acceptance/agency) which will be analysed to assess changes in patterns of emotion expression over time including emotion types and frequency.^37^Thematic analysis will be applied to psychological formulations of ‘schema modes’ constructed by participants during therapy as compared against those endorsed in a quantitative measure (SMI-ED^30^). This will enable us to improve the SPEAKS intervention based on the most salient schema modes, and mode changes associated with better outcomes.

Participants may participate without agreeing to their formulations or therapy recordings being analysed.

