## Methods: data collection, management and analysis

### Allocation, allocation concealment and blinding

Not applicable due to the single arm design.

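### Developers score fidelity on recordings from therapy that developers supervise, with no rule keeping the two roles apart, and one arm is given as the reason for no blinding although raters and coders can still be masked

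*Protocol article*

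**What the plan says.** All references are to the protocol article.

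- **Who rates fidelity** (Measures of adherence and compliance): "A random selection of therapy tapes will be assessed for fidelity and adherence to the model judged by the intervention developers". The items are therapist empathy, on a named scale, and whether therapeutic tasks were suitably chosen and suitably resolved.
- **Who supervises** (Therapist training and supervision): "Ongoing fortnightly supervision is delivered by SPEAKS developers".
- **Where the tapes come from** (same section): "Where participants consent, all therapy sessions are video recorded for supervision".
- **What supervision is for** (Treatment fidelity, untoward events and protocol adherence): "Reviewing videotaped sessions in supervision ensures competent treatment delivery adhering to the SPEAKS model".
- **Blinding** (Allocation, allocation concealment and blinding): the whole entry is "Not applicable due to the single arm design".
- **Change process** (Measures of SPEAKS Change Process): "Videoed therapy sessions will be analysed according to two coding systems to better understand change associated with better clinical outcomes". The coding is also meant to test what changes and in which sequence. Formulations of schema modes are also analysed thematically.
- **Coders** (Availability of data and materials): trainee psychologists, who do not know who the participant is except through what the recording shows. Masking to outcome is not mentioned.

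**The concern.** Two features of the plan weaken the observer-rated evidence.

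First, the article relies on developer supervision to secure adherence and then has developers grade whether adherence was secured, using the same pool of recordings. Empathy, task choice and task resolution all call for a rater's discretion. Someone who has helped to steer a case is not well placed to give a detached score for it.

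Second, the reason given for having no blinding covers only part of what blinding means. The change-process work asks whether coded events come in a predicted order and whether they go with better outcome. A coder who knows how the participant fared, or which session is on screen, could let that knowledge into the codes being compared.

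At stake is how much weight favourable findings can bear on two of the four hypotheses under Objectives: that therapists and service users can adhere to the model and the research requirements, and that change follows the proposed process. Under Potential implications, the article says the study will inform progression to larger trials and refinement of the therapy.

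**Working it through.** The article states no figure for rating bias, so the check is a reading across sections.

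**1. Are raters and supervisors the same people?** The fidelity section names the developers as raters. The training section names developers as supervisors. The Speaks intervention section describes the supervisors more loosely: "Therapists receive fortnightly supervision by supervisors trained in the supervision requirements of SPEAKS". That wording fits the training section, which is the more specific of the two. Both tasks therefore fall to one group, and the Intervention development section lists three developers.

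**2. Do they work from the same recordings?** Consented sessions are recorded for supervision, and the fidelity sample is drawn at random from the session recordings. The pool is shared. It does not follow that a given sampled tape was watched in supervision: therapy is weekly and supervision fortnightly, and the article does not say which tapes are reviewed there.

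**3. Does any rule separate the roles?** None is stated. Random selection governs which tapes are scored, not who scores them.

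**4. Does a single arm make blinding inapplicable?** Taking the parts of the heading in turn:

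| Element | Removed by having one arm? |
|---|---|
| Allocation | Yes |
| Allocation concealment | Yes |
| Blinding to allocated treatment | Yes |
| Masking raters or coders to outcome | No |
| Masking coders to session position | No, though content will partly reveal it |

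**5. Is coder masking to outcome secured elsewhere?**
- Data management and availability holds back post-treatment data until database lock and gives access to the final dataset to the principal investigators and research assistant. It does not say that coding must finish before lock. It also does not cover the 3-, 6- and 9-month scores listed under Participant timeline, or completion status.
- Data analysis includes clinical psychology trainees among those who analyse the data.
- The position is therefore undetermined: masking to outcome is neither secured nor shown to be absent.

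**6. What else supports the two hypotheses?**
- Adherence: treatment length, session numbers and content; a case record of phase, emotions and tasks for each session; completeness of measures.
- Change process: clinical and emotion questionnaires every 3 months, including six intervention-specific instruments, and a comparison of formulations with a questionnaire measure of schema modes.

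**7. Do the plan's own figures depend on the ratings?** No. Recruitment is 36 / (1 − 0.40) = 60. The drop-out precision is 1.96 × √(0.40 × 0.60 / 36) = 0.160, that is ±16%. Both reproduce and neither uses a rating. The power analysis for the next trial uses EDEQ change.

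**The case against.** The strongest reply has four parts.

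**Already disclosed.** The strengths and limitations list concedes non-blinded procedures and possible allegiance effects. This is true, and it shows that nothing is hidden. Conceding a bias does not control it, however, and the Data analysis section orders the acceptability analyses specifically to avoid bias, so the sponsor accepts procedural safeguards of this kind.

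**A condensed article.** Detailed masking procedure may sit in the full protocol. That stands against any claim that coders are unmasked. It does not rescue the reason the article does give, which fails for rater masking whatever the full protocol contains, nor the stated choice of developers as raters.

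**Developers know the model best.** In a first feasibility test of a new integrative therapy this is a defensible choice. It supports using developers as raters, but not letting a developer rate a case that he or she supervised.

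**Other evidence exists.** This stands, and it limits the point to one strand of evidence.

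A reader might also infer more than the text supports:
- *That developers do grade their own supervised cases.* The article does not say who rates which tape. It only leaves this open.
- *That developers wrote the guidebook and delivered the training.* No author or trainer is named for either.
- *That the two hypotheses are decided on these ratings alone.* The other sources listed above contradict this.
- *That the inflation in reported adherence can be quantified.* The article gives neither a rate nor a threshold from which to do so.

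**Conclusion.** The point holds in limited form. As written, the plan allows a developer to score fidelity for a case that he or she supervised, and it dismisses blinding for a reason that applies to allocation but not to raters or coders. The only coder masking stated is to identity.

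The likely direction of any bias is towards the model. Its size cannot be estimated from the document. The conclusion rests on reading the training section literally, so that developers are the supervisors, and on there being no separation rule outside this article. If the full protocol contains one, what remains is to correct the blinding entry and report the rule.

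The trial remains valid for its feasibility aims, and the EDEQ-based sample-size estimate is untouched. Without the change, favourable fidelity and video-coding results should be read as supportive rather than independent evidence. The change is worth making because it is cheap.

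**What to change.** **Measures of adherence and compliance.** Add: *No developer rates a tape from a therapist or participant whom that developer supervised; such tapes go to another of the existing developers. Raters do not see outcome scores.*

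**Allocation, allocation concealment and blinding.** Limit the not-applicable statement to allocation and allocation concealment, and add: *Coders of sessions and formulations do not see EDEQ, BMI or completion status until their codes are locked. Session numbers are removed from file labels where practicable.*

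**Cost.** Some reassignment of tapes, relabelling of files and a dated lock on the codes, using the existing developers and trainees. The article does not say which developer supervises whom, so the sponsor should confirm that a free rater exists for each case. If supervision is shared so widely that none does, that should be stated when fidelity is reported.

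**What it does not solve.** Session content will often reveal the phase of therapy, so masking to session position is only partial. Exchanging tapes removes self-grading but not developers' allegiance to the model, which should stay in the limitations.
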